### Sample size

On the basis of the literature, an increase in bacterial growth of 100 colony-forming units (CFUs) per plate will be considered clinically significant [32]. For a statistical power of 95% and an alpha test risk of 5%, the sample size has been estimated to be 48 patients per study arm.

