### Group assignment, randomization and allocation concealment

Patients will be randomly allocated to group I (n = 48), in which the dressing will be removed on the first postoperative day, or group II (n = 48), in which the dressing will be removed on the sixth postoperative day. Allocation will be determined by a random, computer-generated sequence (Bioestat 5.0, Instituto Mamirauá, Belém, PA, Brazil). An opaque envelope with the patient number will be opened on the first postoperative day to reveal the allocation of the patient.

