### Assessment of postoperative infections and dressing duration

Patients will be evaluated weekly for four weeks, and then re-evaluated at six months and one year after the operation. The CDC definition and classification of SSIs will be used. As the surgery involves the implantation of prostheses, an SSI is defined as an infection that occurs within one year after the surgery [37]. The patients will use a five-point scale to classify the dressing in terms of comfort, practicality and safety. This assessment will be done at the postoperative week two visit for each patient.

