### Outcomes

The primary outcome will be cutaneous colonization, expressed as the number of CFUs. The incidence of SSI and the perceptions of patients towards healing will be secondary outcomes. Participation will be completed at one year after surgery, after evaluation for the presence of infection.

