### Statistical analysis

The Mann–Whitney U test will be used to test the homogeneity of the groups in terms of age, BMI and duration of surgery. The Friedman test will be used to compare the number of CFUs in the samples collected before, and one and six days after the application of the dressing in group I. If there is a significant difference between these times, then the Friedman test will be supplemented with the multiple comparisons test to determine at which time points significant differences appeared. In group II, the Wilcoxon test will be used to compare the number of CFUs in samples collected before the dressing and on the sixth postoperative day. The Mann–Whitney U test will be used to compare groups I and II in terms of the number of CFUs before and six days after the application of the dressing. Tests will always be applied independently for each medium used.

The Fisher test will be used to compare groups I and II in terms of the rates of infection. The Kolmogorov-Smirnov test will be used to compare the two groups in terms of the perceptions of the patients regarding the comfort, safety and practicality of the dressings. All statistical analyses will be performed using SPSS software (version 18, SPSS Inc., Chicago, United States of America). A *P* value ≤0.05 will be considered to be statistically significant.

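### With its usual large-sample P value, the Kolmogorov-Smirnov test on five-point dressing ratings has an actual size below 1% at 48 per arm and is likely to miss moderate differences

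*Protocol article*

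**What the plan says.** All places are in the protocol article.

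- Assessment of postoperative infections and dressing duration: "The patients will use a five-point scale to classify the dressing in terms of comfort, practicality and safety". The ratings are taken at the week-two visit.
- Statistical analysis: "The Kolmogorov-Smirnov test will be used to compare the two groups in terms of the perceptions of the patients", covering the same three ratings. The criterion is: "A *P* value ≤0.05 will be considered to be statistically significant". The software is SPSS version 18. The section does not say whether the Kolmogorov-Smirnov P value is asymptotic, exact or permutation-based.
- Group assignment, randomization and allocation concealment: 48 patients in each group.
- Sample size: the 48 per arm rests on colony counts only. No effect size or power is given for the ratings.
- Outcomes: "the perceptions of patients towards healing will be secondary outcomes". The Abstract, Study aims, Assessment and Statistical analysis sections instead concern perceptions of the dressing.

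**The concern.** The Kolmogorov-Smirnov statistic D is the largest gap between two cumulative distributions. Its usual P value is derived for a continuous variable, where the gap can peak at any observed value. On a five-point scale, up to 96 ratings fall on five values, so the gap can occur at only four cut-points. The continuous-data reference distribution then overstates how large D tends to be by chance, and the test rejects less often than its nominal level.

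Patient perception is a declared secondary aim. The Background section frames it as a preference for one dressing duration, citing a breast-reduction study in which patients preferred six days. If the large-sample P value is used, a moderate preference could easily go undetected, and a non-significant result would say little.

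**Working it through.** **Inputs.** From the protocol: 48 per arm, five ordered categories, significance at P ≤ 0.05. Assumed: two-sided testing, all 48 patients per arm rated, and the response distributions below, because the protocol gives none. The protocol states no power for the ratings, so there is no figure of its own to reproduce on this point.

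**Step 1: rejection threshold.** The large-sample statistic is Z = D × √(n₁n₂/(n₁+n₂)) = D × √(48×48/96) = D × √24, with P ≈ 2·exp(−2Z²).

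- D = 13/48 = 0.271: Z = 1.327, P = 0.059, not significant.
- D = 14/48 = 0.292: Z = 1.429, P = 0.034, significant.

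The counts at or below some cut-point must therefore differ by at least 14 patients.

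**Step 2: hand check of the size.** Under no difference, with true cumulative proportion p at a cut-point, the difference in counts has variance 2×48×p(1−p). With a continuity correction (13.5 in place of 14):

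- p = 0.5: variance 24, SD 4.90, 13.5/4.90 = 2.76, two-sided probability about 0.006.
- p = 0.3 (70% in the top category): variance 20.16, SD 4.49, ratio 3.01, about 0.0026.
- p = 0.2 (80% in the top category): variance 15.36, SD 3.92, ratio 3.44, about 0.0006.

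These are single cut-point values. The other cut-points add something, but they are few and correlated.

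**Step 3: simulated size** (200,000 null trials per five-category distribution; category probabilities run from lowest to highest).

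| Assumed distribution | KS, large-sample P | Mann-Whitney, tie-corrected |
|---|---|---|
| Uniform (0.20 each) | 0.0092 | 0.050 |
| Bell (0.10, 0.20, 0.40, 0.20, 0.10) | 0.0048 | 0.049 |
| Moderate skew (0.05, 0.10, 0.20, 0.35, 0.30) | 0.0060 | 0.049 |
| Skew (0.02, 0.05, 0.13, 0.30, 0.50) | 0.0066 | 0.050 |
| Ceiling (0.01, 0.02, 0.07, 0.20, 0.70) | 0.0026 | 0.050 |
| Stronger ceiling (0, 0, 0.05, 0.15, 0.80) | 0.0004 | 0.049 |

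On untied continuous data at 48 per arm the same Kolmogorov-Smirnov test has size 0.032 (20,000 trials). Part of the shortfall from 0.05 therefore exists without ties; most of it comes from ties.

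**Step 4: power** (proportional-odds shift, 40,000 trials per scenario; 3,000 trials with 1,500 permutations each for the permutation version). Off the ceiling means the first four distributions in the table above.

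| Scenario | KS, large-sample | KS, permutation | Mann-Whitney |
|---|---|---|---|
| OR 2, off the ceiling | 0.12–0.19 | 0.32–0.37 | 0.40–0.47 |
| OR 3, off the ceiling | 0.38–0.55 | 0.66–0.74 | 0.74–0.84 |
| OR 5, off the ceiling | 0.72–0.92 | 0.92–0.97 | 0.95–0.99 |
| OR 2, 70% in top category | 0.03 | 0.21 | 0.30 |
| OR 3, 70% in top category | 0.10 | 0.48 | 0.57 |
| OR 5, 70% in top category | 0.21 | 0.75 | 0.82 |

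Matched by distribution, the loss from the large-sample test against Mann-Whitney at OR 2 to 3 off the ceiling is about 28 to 40 points. The smallest is the skewed case at OR 2 (0.401 − 0.123 = 0.278) and the largest the bell case at OR 2.5 (0.690 − 0.288 = 0.402). In the ceiling case it is 0.567 − 0.096 = 0.471 at OR 3 and 0.818 − 0.214 = 0.604 at OR 5.

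The permutation version has size 0.028 to 0.035.

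**Step 5: a case that favours Kolmogorov-Smirnov.** For a pure difference in spread, (0.30, 0.15, 0.10, 0.15, 0.30) against (0.05, 0.20, 0.50, 0.20, 0.05), the large-sample Kolmogorov-Smirnov test has power 0.71 and Mann-Whitney 0.07.

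**The case against.** The strongest objection is that the sub-1% size is conditional. The article does not specify the P value, and that detail may sit in a fuller plan that is not shown. This stands: a reader might infer that the trial does test this aim below 1%, and the text does not establish that. The recommendation survives, because even with a permutation P value Mann-Whitney has more power in every shift scenario examined.

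A reader might also infer that real differences will be missed outright. That goes too far: off the ceiling, a shift of OR 5 is still detected with power 0.72 to 0.92. The documents give no expected size for the preference, so they do not show that OR 2 to 3 is the relevant range.

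Nor is it right that the test ignores the order of the categories. It compares cumulative proportions, which depend on order; its weakness here is low power against a shift. For a spread difference it is the better test, and the Statistical analysis section names no location parameter. Against that, the Background section describes perception as a preference for one duration, which is a shift.

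Finally, the error is conservative, so it creates no excess of false positive claims, and nothing in the article says that a non-significant result will be read as equivalence. Both points stand and limit the weight of the concern.

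**Conclusion.** The point holds in conditional form. If the large-sample P value is used, the Kolmogorov-Smirnov test on these ratings has an actual size of about 0.04% to 0.9% and loses about 28 to 40 points of power for moderate shifts off the ceiling, and 47 points at OR 3 when ratings cluster in the top category. Moderate differences in this secondary outcome are then likely to be missed. With a permutation P value the size is about 0.03, and the loss at OR 3 shrinks to about 8 to 13 points.

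The rejection threshold follows directly from 48 per arm. The size and power figures rest on assumed response distributions and proportional-odds shifts, though the direction was the same in every shift scenario. The primary outcome and the sample size are not affected.

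The reference to healing in the Outcomes section is a separate editorial inconsistency. No healing rating is described elsewhere and the intended outcome is clear from the other sections, so it adds nothing to the argument about the test.

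**What to change.** In Statistical analysis, replace the Kolmogorov-Smirnov test with the tie-corrected Mann-Whitney U test, or a proportional-odds model, for each of the three ratings. Report the common odds ratio, or the probability that a rating in one group is better than in the other, with a 95% confidence interval. If Kolmogorov-Smirnov is kept, state that its P value will be obtained by permutation.

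The cost is one sentence, with no new data. Mann-Whitney is already used elsewhere in the plan. The price is lower sensitivity to a pure difference in spread; showing the full distribution of ratings by group would let a reader see one. Trial status reports 69 of the planned 96 patients enrolled, so the change can be made before the final analysis.

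Separately, change the wording in Outcomes so that the secondary outcome is perception of the dressing (comfort, practicality, safety), in line with the other sections.

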## Discussion

As breast augmentation with silicone implants has become a common procedure, risks factors for complications associated with this procedure must be investigated in detail to improve procedural safety. As modern protocols and guidelines should be based on the principles of evidence-based medicine, well-designed randomized clinical trials are essential to guide or adjust clinical practice [28].

Attention to the skin incision in breast augmentation is warranted, as this incision acts as a gateway for microorganisms present on the surrounding skin or in external sources of contamination. Incisions for insertion of breast implants are most commonly placed in the inframammary fold, areola or axilla [38,39]. Each of these different incisions traverse through the breast ducts at different levels, providing for different potential amounts of contamination by breast duct bacteria-colonized material [40]. However, there is not a clear relationship between incision location and SSI, and literature on this issue is controversial. Wiener, in a review of 430 patients who underwent augmentation surgery, found a significantly higher incidence of capsular contracture when a periareolar incision was used, and he hypothesized that this could be due to bacterial contamination from contact with the endogenous bacteria within the breast tissue [40]. Jacobson *et al*., in a retrospective chart review of 197 primary breast augmentation patients, observed that transaxillary incisions produced the highest incidence of contracture (6.4%), followed by periareolar (2.4%) and inframammary (0.5%), with a statistically significant difference [41]. Stutman *et al*. performed a chart review on 619 patients who underwent primary breast augmentation, and found a trend of increased rate of capsular contracture when the inframammary incision was used, but this was without statistical significance [39]. The inframammary incisions have been the most commonly used for primary augmentation mammaplasty, since it is the simplest and most straightforward approach [38-40]. For this reason, this was the incision of choice for the current trial.

The use of biomaterials and the increased pathogenicity of bacteria enable colonization of the implant even when the bacterial load is relatively low. It is exceedingly difficult to control bacterial growth after implant colonization has occurred, and this difficulty tends to increase the infection risk [4]. Subclinical implant infection is related to the development of bacterial biofilms and severe capsular contracture around the implant, which are the leading causes of reoperation in breast augmentation [19]. The need to remove the implant can cause psychological trauma to the patient [2]. For these reasons, implant subclinical infection has become a focus of substantial research [19,20].

Bacteria are responsible for most postoperative infections that occur after breast augmentation when implants are used. Gram-positive cocci are part of the skin flora, especially in the upper portion of the trunk, and they account for many implant-related SSIs [42]. Cultures of mammary tissue collected during breast surgery demonstrate that these bacteria are the most frequent endogenous bacteria in the breasts [18]. Infections by opportunistic agents, such as fungi, Gram-negative bacteria and atypical mycobacteria, have also been described [43-45]. Therefore, we have opted to culture these organisms as well.

An important component of SSI prevention is to minimize all possible risk factors. The application of postoperative dressing plays a key role in this endeavor [12]. However, it is difficult to demonstrate gains related to the use of dressings for ensuring clean wounds and lowering the infection rate [46]. For this reason, we chose the rate of skin colonization, which is related to the SSI rate [4,11,13,14], as the primary focus of this study.

The opinion of the patients regarding the proposed treatment is an important factor in the quality of care. Two different surgical dressing strategies are proposed, and determining patients’ perceptions regarding their comfort, convenience and safety is a secondary goal of this study. The results of this clinical trial may help to standardize postoperative wound care after breast augmentation with silicone implants.

## Trial status

Recruitment began in April, 2012. A total of 69 patients have been enrolled in this study and have undergone breast augmentation with silicone implants. All patients will be monitored for the presence of infection until one year after their operation.

## Abbreviations

BMI: Body mass index
CDC: Centers for Disease Control and Prevention
CFU: Colony forming units
SSI: Surgical site infection
